## Abstract

**Background:**

The present study protocol describes the trial design of a primary care intervention cohort study, which examines whether an extended, multi-professional physical activity referral (PAR) intervention is more effective in enhancing and maintaining self-reported physical activity than physical activity prescription in usual care. The study targets patients with newly diagnosed hypertension and/or type 2 diabetes. Secondary outcomes include: need of pharmacological therapy; blood pressure/plasma glucose; physical fitness and anthropometric variables; mental health; health related quality of life; and cost-effectiveness.

**Methods/Design:**

The study is designed as a long-term intervention. Three primary care centres are involved in the study, each constituting one of three treatment groups: 1) Intervention group (IG): multi-professional team intervention with PAR, 2) Control group A (CA): physical activity prescription in usual care and 3) Control group B: treatment as usual (retrospective data collection). The intervention is based on self-determination theory and follows the principles of motivational interviewing. The primary outcome, physical activity, is measured with the International Physical Activity Questionnaire (IPAQ) and expressed as metabolic equivalent of task (MET)-minutes per week. Physical fitness is estimated with the 6-minute walk test in IG only. Variables such as health behaviours; health-related quality of life; motivation to change; mental health; demographics and socioeconomic characteristics are assessed with an electronic study questionnaire that submits all data to a patient database, which automatically provides feed-back to the health-care providers on the patients’ health status. Cost-effectiveness of the intervention is evaluated continuously and the intermediate outcomes of the intervention are extrapolated by economic modelling.

**Discussions:**

By helping patients to overcome practical, social and cultural obstacles and increase their internal motivation for physical activity we aim to improve their physical health in a long-term perspective. The targeted patients belong to a patient category that is supposed to benefit from increased physical activity in terms of improved physiological values, mental status and quality of life, decreased risk of complications and maybe a decreased need of medication.

## Background

The present protocol describes the trial design of a Swedish primary care intervention cohort study, which examines whether an extended, multi-professional physical activity referral (PAR) intervention is more effective in enhancing and maintaining the level of physical activity than physical activity prescription in usual care. The target group is patients with newly diagnosed type 2 diabetes and/or hypertension. The study is designed as a long-term intervention with recurrent analyses of self-reported physical activity levels as well as the effects of physical activity on health-related variables and cost-effectiveness.

Hypertension and type 2 diabetes belong to the major risk factors for cardiovascular disease that can be modified by a change in lifestyle, such as increased physical activity [1-3]. Several studies confirm that physical activity reduces the systolic and diastolic blood pressure in patients with hypertension, and improves the glycemic control in subjects with type 2 diabetes [2,4]. The evidence suggests that lifestyle modifications and exercise therapy are as effective as pharmacological treatment in selected cases. According to current guidelines, lifestyle modifications should be the first-line treatment alternative for patients with diagnose, or risk for, type 2 diabetes or hypertension [5,6]. Daily or almost daily aerobic physical activity of moderate intensity, such as brisk walking or swimming, for at least 30 minutes is recommended for both conditions [5-7].

### The extended PAR intervention

Written prescriptions of physical activity — in Sweden commonly referred to as PARs — provide an attractive alternative for encouraging patients to increase their physical activity levels and thereby improve health and quality of life. These prescriptions are provided by registered health care professionals in primary care and hospitals [8,9]. The effectiveness of Physical activity or exercise referrals and exercise referral schemes show mixed results. A review article shows that physical activity referrals and exercise referrals increase the physical activity levels in certain populations, although the effect tends to wear off over time [10]. A more recent review state that uncertainty remains about the effectiveness of exercise referral schemes for increasing physical activity and improving health [11]. The Swedish Council on Technology Assessment in Health Care, SBU, state that advice and counseling of patients increases physical activity by 12–50% for at least 6 months, and that a supplementing prescription can increase the activity even further [12]. Clearly, more research is needed to elucidate predictors of successful adherence to this kind of prescriptions or referrals.

Factors that influence the level of physical activity are often classified as individual (e.g. demography, cognitive skills, self-efficacy), interpersonal (e.g. encouragement from family, friends or care givers) or environmental (e.g. culture, physical surroundings, access). Self-efficacy, self-perceived health status and social support belong to the most important predictors of exercise behavior [13]. Other reasons for performing physical activity include improved appearance, enjoyment of the activity itself, social interaction and stress relief [13,14].

To optimize the adherence to PARs and increase the level of physical activity in patients with newly diagnosed type 2 diabetes or hypertension, we will introduce an extended PAR intervention. The aim is to give the patients sufficient support to become regularly active and prevent relapse into inactivity.

The step-based intervention involves a multi-disciplinary primary care team, which may include e.g. physician, hypertension/diabetes nurse, psychologist, physiotherapist or occupational therapist. The team will, in consultation with the patient, customize a PAR based on the summarized results of a pre-test, which includes a computerized study questionnaire, a 6-minute walk test, and physiological status. The study questionnaire is designed to capture factors that may impact the level of physical activity such as self-efficacy and general health behaviors [15]. The multi-disciplinary team will use the principles of Self-Determination Theory (SDT) and Motivational Interviewing (MI) throughout the patient meetings to improve the adherence to the intervention.

The suggested PAR concept is somewhat different from the original Swedish PAR schemes, which are written prescriptions of individual activities, such as jogging, or group-based activities, such as aerobics, and commonly designed according to the national recommendations for respective disease. In our extended concept, the PAR is based on the patient’s preferences and interests, physical and mental status, and motivation.

### Self-Determination Theory (SDT)

SDT is a theory of motivation, which was initially developed by Deci and Ryan [16,17]. SDT focuses on internalization of motivation in order to increase qualities such as perseverance [18], which is crucial for maintenance of profound lifestyle changes. SDT defines 3 innate psychological needs that are crucial for internalization of motivation: *autonomy*, *competence* and *relatedness*[17,18]. Satisfaction of these 3 needs improves the internalization of motivation along a continuous scale that extends from *amotivation* (lack of intention to act), over *extrinsic motivation* (when the activity is performed to achieve outcomes that are separable from the behaviour itself), to *intrinsic motivation* (which comes from the satisfactions of the behaviour itself) [16,17] (Figure 1). As can be seen in Figure 1, extrinsic motivation is divided into 4 subgroups: *external regulation*, *introjected regulation*, *identified regulation* and *integrated regulation*[16,18]. Thus, the patients’ motivation can move stepwise within extrinsic motivation.

**Figure 1 F1:**
[figure not shown]
**The Self-determination continuum.** The figure shows the different types of motivations, regulations and loci of causality according to SDT. One of the aims is to evaluate the patients’ degree of internalization at baseline and changes in along the continuum during the course of the study. Adapted from [17,18].

### Motivational Interviewing (MI)

The 3 innate psychological needs *competence*, *autonomy*, and *relatedness*, defined by SDT, are believed to be promoted by 3 environmental factors: *structure, autonomy support and involvement*[19]. These 3 environmental factors can in turn be supported by MI. MI is a client-centred counselling style that aims to elicit behaviour changes by helping clients to explore and resolve ambivalence [19,20] (Figure 2). The general principles of MI have been shown to correspond very well with the intentions of motivational internalization in SDT: whereas SDT provides a theoretical framework for internalization of motivation, MI is more practically oriented and can help to translate the SDT concept into practice [19,21].

**Figure 2 F2:**
[figure not shown]
**Correlation between Self-determination theory and Motivational Interviewing.** Adapted for PAR intervention from [19].

The principles of MI have previously been shown to be effective in improving health behaviours such as diet, exercise and addiction treatment [21].

### Health economic aspects

One of the main priorities of Sweden’s National Public Health Policy is to increase the level of physical activity in the population and a systematic literature review published by the Swedish Council on Technology Assessment in Health Care points to health economic evaluations of physical activity intervention as one area of special importance in future research. This taken together with the relatively scarce, and of varying quality, health economic studies on interventions promoting physical activity that exists today, makes this field of special importance. Economic evaluation of interventions to improve the management of diabetes have, in recent years, increasingly relied on modelling of long term outcomes and costs of disease [22]. Simulation models in diabetes typically project both life expectancy and the degree of morbidity associated with the disease. These estimates can assist in resource planning and can be used to inform economic evaluations, as they quantify potential savings that accrue when interventions reduce the risk of diabetes-related complications. Currently many diabetes simulation models use annual cycles to predict a profile of events over time [23,24]. The benefits of the present intervention are expected to be found in reduced health care and drug utilisation, and increased productivity (measured as reduced sickness absence and increased employment). More specifically, increased physical activity is expected to, among others, reduce the risk of cardiovascular diseases and improve health related quality of life.

### Aims

The first aim of the study is to examine whether an extended multi-professional PAR intervention, based on SDT, is effective in increasing and maintaining the self-reported physical activity level in patients with newly diagnosed type 2 diabetes or hypertension or both.

The second aim is to evaluate changes in a number of health-related variables such as blood pressure, plasma glucose, need of pharmacological therapy, health related quality of life, anxiety and depression, behavioral predictors, physical fitness, obesity, and activities of daily living.

The third aim is to perform an economic evaluation of the intervention from a societal perspective to allow for efficient use of societal resources.

## Methods/design

The study was initiated by Dalby health care centre and involves three primary care centres in Skåne, southern Sweden. Each primary care centre in Sweden has a population of listed patients; the 155 primary care centres in Skåne have between 3000–15500 listed patients and 10–40 employees, e.g. physicians, nurses, physiotherapists, occupational therapists, dieticians, and behavioural scientists.

In the present study, each of the three primary care centers constitutes one of three treatment groups: 1) Intervention group: extended PAR intervention based on a multi-professional team analysis of the study questionnaire and a 6-minute walk test, 2) Control group A: study questionnaire and physical activity prescription in usual care and 3) Control group B: treatment as usual (retrospective data collection). The two control primary care centres have similar socioeconomic and living environment profiles as the Intervention centre. At the health care centres in the Intervention group and Control group A, all patients with newly debuted type 2-diabetes or hypertension will be continuously asked to participate by their general practitioners (GPs).

The study is designed as a long-term intervention that will extend over several years with regular analyses of the patients’ self-reported physical activity levels, health-related variables and cost-effectiveness.

All parts of the study will be conducted according to the principles of the Helsinki Declaration. Written, informed consent will be obtained from all patients entering the Intervention group or Control group A before inclusion.

### The 5 A’s model

The study will be performed according to the 5 A’s model, which has been the basis for many health behavior change programs [25] and is especially effective for long-term interventions [26]. The model comprises the following 5 steps: Assess; Advice, Agree; Assist; and Arrange, which are continuously followed-up in relation to a personal action plan The contents of each step are presented in Figure 3.

**Figure 3 F3:**
[figure not shown]
**The 5 A’s model.** Adapted for the extended PAR intervention from [25,26].

The 5 A’s will, in our approach, involve the whole primary care team as well as the patients; different parts of the model will be performed by different team members and some parts may even involve family members or local public health and sports organizations.

### Intervention

A flowchart describing the time course of the study for the Intervention group and Control group A is presented in Figure 4. Below follows a short description of the intervention.

**Figure 4 F4:**
[figure not shown]
**Study flowchart.** Flowchart describing the study-specific patient visits. In addition to the study-related visits, the patients will be called to routine visits at the health care centers regularly for blood pressure and plasma glucose check-ups. The flowchart does not include Control group B, which will be analyzed retrospectively. Abbreviations: GP = general practitioner; PAR = physical activity referral.

#### Intervention group

Eligible patients in the intervention group that consent to take part in the study will go through an extensive intervention program, in which a prescription of physical activity (PAR) will be the central part. At the *Baseline visit*, the patient meets his/her GP and a nurse. Values for blood pressure (in sitting position after 5 minutes rest; mean of two measurements, supplemented with 24 hour blood pressure monitoring), body mass index (BMI), and abdominal and hip circumference will be taken and a routine heart and lung auscultation and electrocardiography (ECG) will be performed. Furthermore, the patients will fill in an electronic study questionnaire regarding current health status, including variables such as level of physical activity; health behaviours; stress and anxiety; behavioural predictors; health related quality of life; sleeping habits; and activities of daily living ability. The patients will also perform a 6-minute walk test according to a separate, standardized protocol and guided by a physiotherapist. Fasting plasma glucose and other study specific blood samples will be taken in the morning within a few days.

These measures are in accordance with the first and part of the second step of the 5 A’s model (Figure 3).

After the baseline visit, the patients will be referred to an *Initiation visit* with one or more members of the multi-professional team comprising psychologist, physiotherapist, occupational therapist, physician and nurse as applicable. The initiation visit will take place within 3 weeks from the baseline visit.

The visit will be based on a team discussion regarding the results of the extended screening including the study questionnaire, the 6-minute walk test and baseline values. It will be structured according to step 2–5 in the 5 A’s model (advise, agree, assist and arrange; Figure 3) to provide the patients with a personal action plan based on individual goals and strategies to overcome personal barriers to physical activity. The initiation visit will be founded on the patients’ present level of motivation for exercise: amotivation, extrinsic motivation or intrinsic motivation, as described in the SDT model (Figure 1). To improve the patients’ autonomy, competence and relatedness regarding a more active lifestyle, the team uses the MI-technique throughout the conversation (Figure 2). It should be noted that all prescribers have attended at least one course in MI*.* The resulting action plan may include referrals to specialists (psychologist, physiotherapist and/or occupational therapist) for individual consultations and treatments to improve internal motivation and/or physical abilities. The discussion will result in a customized PAR, usually prescribed by a psychologist or physiotherapist from the team together with the patient. The PARs will be tailored to fit the patients’ physical and mental condition and motivation, and the recommendations in the Swedish report Physical activity in prevention and treatment of diseases, FYSS, as applicable [27].

#### Control group A

The patients in Control group A will go through the same physical examinations and study questionnaire as the patients in the Intervention group at the baseline visit. Apart from this, they will get treatment as usual including physical activity prescription as applicable. For Control group A, this is the only study-related visit during the initiation period. They will not attend an additional initiation visit, perform the 6-minute walk test or get a multi-professional team opinion on their treatment.

#### Follow-up visits

The patients in the Intervention group and Control group A will return to the clinics for follow-up of the study results regularly (Figure 4). During these follow-up visits, a physical examination, including monitoring of blood pressure and fasting plasma glucose and, if required, a heart- and lung auscultation will be performed. BMI, abdominal and hip circumference will be measured and the patients will fill in the same study questionnaire as before or a short version of the study questionnaire, including questions about their activity level. The patients in the Intervention group will also perform regular 6-minute walk tests.

The multi-professional team will, together with the patient, follow up adherence to the physical activity prescription, and modify it if necessary.

#### Routine visits

In addition to these study-related visits, the patients will, if necessary, be called to routine visits at the health care centers for blood pressure and plasma glucose check-ups regularly.

#### Control group B

The patient data in Control group B will be collected from the medical records of patients, diagnosed during the same time period as the other two groups, retrospectively. The same baseline data will be collected as in the other two groups, i.e. time to initiating pharmacological treatment, number of medications and laboratory as well as clinical data. The data will be collected on a population basis.

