### Statistical analysis and power calculation

The first statistical analyses and compilation of results will be performed 18 months after inclusion of the first patient or when the Intervention group and Control group A have included and followed up 60 and 30 eligible patients respectively for at least six months. At that point, data will also be collected retrospectively in control group B. Reasons for non-attendance in the study will be analyzed as well as reasons for non-adherence to the intervention. Allocation will be concealed, and study data blinded, for the bio-statisticians and researchers who will perform the analyses.

The sample size is based on an assumed statistical power of 80%, a significance level of 5%, a difference of 200 MET-minutes between the groups, a standard deviation of 300 MET-minutes and a worst-case loss to follow-up of 30%.

The secondary outcomes blood pressure, plasma glucose, need of pharmacological therapy, and cost-effectiveness will be compared between all three study groups.

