## Discussion

The targeted patients – individuals with newly diagnosed type 2 diabetes or hypertension – belong to a patient category that is indeed supposed to benefit from increased physical activity in terms of improved health variables, decreased risk of complications [27], and possibly also a decreased need of pharmacological therapy [42]. In the present study we combine a patient-centered lifestyle modification by a multi-professional team; a theory-based approach for self-regulation and behavior change; a feedback system for immediate response to treatment and adherence to treatment; and determination of cost-effectiveness of the intervention. This is in agreement with current guidelines for the prevention and management of the targeted diseases [5,6], and may increase the efficiency of treatment and evaluation of intervention.

The intervention intends to increase the patients’ internal motivation for physical activity by following the principles of SDT and MI, and thereby improve their adherence to PAR. The ultimate goal is to decrease cardiovascular complications, improve quality of life and work ability and decrease the need of medication. Our hypothesis is that the proposed PAR intervention is a more effective way to support patients in achieving and maintaining a beneficial level of physical activity than treatment as usual. We also believe that this structured intervention can be cost effective if it leads to a better health status and, subsequently, a less need of medical care among these patients.

The reason for using two control groups is that we believe there is a risk that the patients in Control group A may get an increased awareness of physical activity and subsequent alteration of habits, just by participating and filling in the questionnaires. Therefore we are also making a retrospective analysis at a third centre.

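### Three-group comparisons set consenting, study-measured patients against a medical-record cohort, so the Control group B contrasts are confounded, and that cohort cannot show a change in the primary outcome

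*Protocol article*

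**What the plan says.** Under Methods/design, each of three primary care centres forms one group. At the IG and CA centres, "all patients with newly debuted type 2-diabetes or hypertension will be continuously asked to participate by their general practitioners", and "Written, informed consent will be obtained from all patients entering the Intervention group or Control group A before inclusion".

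The Intervention group section standardises baseline blood pressure (seated, rested, "mean of two measurements, supplemented with 24 hour blood pressure monitoring"). The Control group A section gives CA the same baseline examinations. Follow-up visits brings both groups back regularly for study examinations, and Laboratory values requires fasting samples at every study visit.

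The Control group B section says that its data "will be collected from the medical records of patients, diagnosed during the same time period as the other two groups, retrospectively", and adds: "The data will be collected on a population basis". It describes no study visit, measurement standard or consent step for CB.

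Statistical analysis and power calculation then states: "The secondary outcomes blood pressure, plasma glucose, need of pharmacological therapy, and cost-effectiveness will be compared between all three study groups". The Discussion explains that CA patients might become more aware of activity and change their habits through taking part and completing questionnaires: "Therefore we are also making a retrospective analysis at a third centre".

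**The concern.** A comparison across groups is informative to the extent that the groups differ mainly in what was done to them. Here CB also differs from IG and CA in who enters, how values are obtained, and how often patients are seen. Each of these differences runs along the same line as the treatment contrast.

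Two uses of CB are at stake. The first is as a treatment-as-usual comparator for IG on blood pressure, glucose, drug therapy and cost. The second is as a check on whether participation changed CA. A difference in either contrast, or the lack of one, could be read as evidence about the intervention or about participation when it reflects the way the groups were assembled. Drug starts are particularly exposed, because a patient with scheduled study checks has more occasions on which a high value is seen and acted on than one with routine contact only.

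**Working it through.** The plan gives no figure for the CB contrasts. The only group sizes stated, 60 in IG and 30 in CA, are the trigger for the first analysis. The sample-size assumptions concern MET-minutes, and no number is given for CB. The check is therefore a side-by-side reading.

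| Feature | IG and CA | CB |
|---|---|---|
| Entry | Asked by the GP; only those giving written consent (Methods/design) | Records of patients diagnosed in the same period, on a population basis (Control group B) |
| Baseline blood pressure | Seated, rested, mean of two, plus 24-hour monitoring (Intervention group; Control group A) | Whatever the record holds |
| Glucose | Fasting sample at all study visits (Laboratory values) | Whatever the record holds |
| Contact | Regular study visits, plus routine visits if needed (Follow-up visits; Routine visits) | Usual care |
| Activity questionnaire | Yes (Assessment of physical activity level) | No |
| Centre | One each | A third |

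**Decomposing the contrast.** The expected IG–CB difference on a secondary outcome is:

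intervention effect + participation effect + S + M + F + C

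- S is consent selection: (1 − c) × (mean in consenters − mean in non-consenters), where c is the proportion consenting.
- M is study measurement minus record measurement.
- F is the effect of contact frequency, beyond what one wishes to call participation.
- C is the centre difference.

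The CA–CB difference has the same form without the intervention effect. The document gives no value for c, the mean difference, M, F or C, so neither the size nor the sign of the bias can be computed.

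**What the document offers on comparability.** It gives similar socioeconomic and living-environment profiles of the centres (Methods/design), the same diagnosis period and the same baseline data items (Control group B), and one diabetes criterion for intervention and control groups (Inclusion and exclusion criteria). The profiles bear on C, and the other items on case definition. None addresses S, M or F, and the limitations paragraph of the Discussion does not mention them.

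**The stated purpose of CB.** The worry in the Discussion is a change in activity habits in CA. Showing it would need an activity measure in both CA and CB, and the questionnaire is assessed in IG and CA only. CB could reflect such a change only indirectly, through clinical outcomes, where CA–CB also carries S, M, F and C.

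**The case against.** The strongest reply is that this is an openly non-randomised three-centre cohort, that CB enters only secondary comparisons, and that covariate adjustment and record windows usually sit in an analysis plan that is not shown. The protocol also plans to analyse reasons for non-attendance, which bears on consent selection. All of this is fair and limits the weight of the point. It does not remove it: source, sampling, comparison and rationale are fixed in the article itself. Adjustment cannot turn record readings into standardised ones or remove unmeasured differences between volunteers and others.

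Several stronger readings are tempting and are not supported:

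- **CB was diagnosed on single readings, or escapes the eligibility criteria.** Nothing says so. Table 1 is headed as the overall criteria of the study and may be meant to cover CB; the Control group B section does not say. That CB patients gave no consent is likewise an inference from consent being described for IG and CA only.
- **A bias of several mmHg from regression to the mean.** Take assumed between-patient SDs of 12–15, visit SDs of 8–12, a clinic mean of 125–135 and a cut-off of 140 mmHg. Halving the visit variance for a mean of two readings gives a gap of 1.7 to 4.6 mmHg against one reading. But the Intervention group section describes both readings at one baseline visit, and averaging within a visit leaves visit-to-visit variance intact. If only an assumed within-visit SD of 3–6 mmHg is averaged, the gap over the same grid is 0.2 to 1.3 mmHg. Even that presumes single-reading baselines in CB, so no mmHg figure should be attached to this point.
- **The protocol claims that CB will measure activity.** It does not. An unexposed comparator on outcomes found in records is a coherent idea. The weakness is that the reason given concerns an outcome CB lacks.

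**Conclusion.** The point holds as a design weakness of the secondary three-group comparisons. As written, IG–CB and CA–CB differences cannot be attributed to the intervention or to participation, because consent selection, measurement method, contact frequency and centre vary with group. CB cannot show whether participation altered CA's physical activity.

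The size and direction are unknown from the document. The conclusion rests on the stated consent, measurement and data-source arrangements, and on reading population-based record collection as having no volunteer filter. A reader might infer that the primary result is undermined as well; it is not by this route, because the activity questionnaire is compared between IG and CA only. The matter should be corrected before CB data are collected, which the plan schedules for the first analysis.

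**What to change.** 1. **Control group B:** state that the inclusion and exclusion criteria of Table 1 are applied to the CB records.
2. **Drug therapy:** take drug starts and number of medications from the medical records at all three centres, over the same windows counted from diagnosis.
3. **Three-group comparisons:** adjust for baseline blood pressure or glucose, age, sex and diagnosis.
4. **Blood pressure and glucose:** keep study-measured values as the main data for IG versus CA. Use record-based values in all three groups as a sensitivity analysis only. The Routine visits section calls patients in only when necessary, so routine readings may be sparse and concentrated in patients thought to need checking.
5. **Discussion, including limitations:** state that CB contrasts are descriptive, remain open to consent selection, and cannot show whether participation changed CA's activity.

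Items 1 to 4 narrow the differences in eligibility, source and measured case mix. They do not remove consent selection or the centre difference, which is why item 5 is needed. The cost is some extra record extraction for about 90 consented patients (60 + 30), a smaller CB if the criteria were not already to be applied, and a few sentences of text.
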